#### Primary and secondary analysis

Analysis will be primarily descriptive and focuses upon estimation with 95% confidence intervals. Continuous variables will be summarised using means and standard deviations (if normally distributed, assessed by inspection of histograms) or medians and interquartile ranges. Categorical data will be reported as numbers and frequencies. We will report the proportion of eligible patients tested in Part 1 and the baseline characteristics including route of sensitisation for patients deemed ineligible for Part 2, eligible and treated, and eligible but not treated in Part 2.

We will compare the overall response rate of all 21 Treg-treated patients with control responses rates from the 9 patients undergoing immune monitoring in Part 1. Mixed effects regression models will be utilised to describe and analyse outcomes measured repeatedly over time, with log or other transformation made where necessary to meet model assumptions.

Whilst every endeavour will be made to minimise missing data it is inevitable that there will be some. We will report this by study group and report reasons for missingness where available. We will report data in accordance with the Intent to Treat Principal where all treated patients are included in the relevant parts of the data analysis but also intend to report subgroup analyses in those patients who complete TR001 administration and those who received only a partial dose of TR001 due to medical reasons (if applicable).

Further detail will be reported in the statistical analysis plan.

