## Methods/ design

### Study design

The trial flow chart is presented in Fig. 1. The study has two parts: Part 1 will be observational to record functional responses by patient peripheral blood mononuclear cells (PBMC) to sHLA from Pure HLA Proteins ® in FluoroSpot assays. The pattern of these responses forms the basis of eligibility to Part 2. The first 9 patients identified as being eligible will undergo baseline immune monitoring for 2 months to inform statistical analysis of primary endpoint. Part 2 is an adaptive, multi-centre, open-label, one-armed, phase IIa clinical trial, based on Simon’s two stage design, with 12 patients treated in stage 1 and 9 treated in stage 2.

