### Trial endpoints

Primary endpoints.

The primary endpoint is to determine the proportion of patients showing suppression of a defined HLA-specific IFNγ/IL-17A dual FluoroSpot response for 2 months post-treatment, compared to the proportion of patients who show the same changes during baseline immune monitoring. The production of only one cytokine (the one positive at enrolment) will need to be suppressed.

Secondary endpoints.

The secondary endpoints are:Proportion of sensitised dialysis patients with unregulated T & B cell anti-HLA responses, identified in Part 1 observations.Duration of suppression of HLA-specific responses by Tregs.Adverse events associated with Treg therapy.The secondary exploratory mechanistic endpoints are:4.Changes in Treg number and phenotype comparing baseline to post-Treg treatment, studied using detailed immunophenotyping performed by flow (and in selected samples where possible mass cytometry) using validated panels and protocols. Correlations between Treg numbers / phenotype and immune reactivity will be sought.5.The changes in HLA Ab profiles measured by Luminex beads will be assessed using samples taken at enrolment to the observational phase in all, then week 1, 4, 8 then 6- & 12-months post-treatment in those receiving Tregs and baseline, week 1, 4, 8 in those undergoing baseline immune monitoring. All time points ± 1 dialysis session with blood taken at the beginning of dialysis.

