### Statistical considerations and analysis

#### Sample Size calculation

Based on our previous experience of numbers of patients presenting anti-donor reactivity without evidence of suppression by CD25^+^ T cells, we have calculated that 100 patients will need to be recruited for Part 1. This number is based on availability of the clinical population in the study sites which is feasible in the study timeframe. For Part 2, Simon’s two-stage design will be used for the trial, with α = 0.05 and 1-β = 90%. Clinical consensus amongst the expert team is that if fewer than 20% meet the primary endpoint there is no merit in further investigating Tregs, whereas if ≥ 50% respond to Tregs further investigation will be merited. Based on these parameters, 21 patients are required, all of whom will be monitored for at least 2 months post-treatment to meet the data collection for the primary endpoint. Of these 21 patients, 12 will be allocated to stage 1 and 9 to stage 2, based on the order of recruitment. At the end of stage 1, data will be assessed for futility using stopping rules based on the clinical consensus: ≥ 6 patients meeting the primary endpoint, stage 2 will commence; ≤ 2 patients meeting the primary endpoint, the trial will stop; 3–5 patients meeting the primary endpoint, the trial will pause for the sample size to be re-estimated after discussion with the funder.

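### The primary endpoint is a comparison of 21 treated with 9 monitored patients, but the stated alpha and 90% power belong to a one-sample Simon rule against a fixed 20%

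*Protocol article*

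**What the plan says.** The article describes the primary question in two ways.

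- **As a comparison.** Under Trial endpoints, the proportion of patients suppressed for two months is "compared to the proportion of patients who show the same changes during baseline immune monitoring". Under Primary and secondary analysis: "We will compare the overall response rate of all 21 Treg-treated patients with control responses rates from the 9 patients" in Part 1 monitoring. That section also calls the analysis mainly descriptive, built on estimates with 95% confidence intervals. It names no two-sample test.
- **As a one-sample rule.** Under Study design, "Part 2 is an adaptive, multi-centre, open-label, one-armed, phase IIa clinical trial". Under Sample Size calculation, Simon's "two-stage design will be used for the trial, with α = 0.05 and 1-β = 90" per cent. The thresholds there are clinical consensus. The lower one reads "if fewer than 20% meet the primary endpoint there is no merit in further investigating Tregs". The upper one is a response rate of 50% or more, which the team regards as enough to carry the work forward. From these the section concludes "Based on these parameters, 21 patients are required", of whom "12 will be allocated to stage 1 and 9 to stage 2, based on the order of recruitment". At stage 1 the trial stops at 2 or fewer of 12, continues at 6 or more, and pauses at 3–5 to re-estimate the sample size.

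The Abstract and the Background give the primary endpoint without any comparator. The Background adds that nobody knows how stable these responses are over time in this population. The nine monitored patients are the first nine found eligible for Part 2, and the Fig. 1 legend says dosing follows the order of eligibility.

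**The concern.** A test of the treated rate against a fixed 20% and a comparison of the treated rate with an observed rate in nine patients are different hypotheses. The first treats the reference as known. The second carries the sampling error of nine patients, for which the sample size makes no allowance. The analysis section describes only the second, so the test for which alpha and power are stated does not appear among the analyses.

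The Background makes separating a Treg effect from spontaneous variation a central question. If the Simon count is positive and the comparison is inconclusive, or the reverse, the article does not say which one decides. An inconclusive comparison could then be read as evidence against Tregs when it mainly reflects nine control patients.

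**Working it through.** **1. Reproduce the stated design.** Inputs from Sample Size calculation: p0 = 0.20, p1 = 0.50, alpha 0.05, power 0.90, n1 = 12, n2 = 9, stop at ≤ 2 of 12. For final bound r,

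P(positive | p) = Σ over x = 3..12 of Bin(x; 12, p) × P[Bin(9, p) ≥ r + 1 − x].

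An exact search gives r = 7, so the result is positive at 8 or more of 21:
- p = 0.20: 0.042 (alpha)
- p = 0.50: 0.901 (power)

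No design with fewer than 21 patients meets both limits. The 21 and the 90% are therefore the minimax Simon design. They contain no term for the nine monitored patients.

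**2. Power of the 21-versus-9 comparison.** The article gives no test and no background rate, so three things are assumed: treated rate 50%, independent groups, Fisher's exact test at 5%. With background rate c,

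Power = Σ over (x, y) of Bin(x; 21, 0.5) × Bin(y; 9, c), summed over tables with p ≤ 0.05.

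| Background rate c (assumed) | Two-sided | One-sided |
|---|---|---|
| 20% | 29% | 30% |
| 10% | 52% | 56% |
| 5% | 66% | 73% |
| 0% | 81% | 91% |

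Other tests at c = 20% give 30% to 34% two-sided (Boschloo, normal approximation, pooled z) and 44% to 49% one-sided.

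**3. Precision, since estimation is the declared aim.** For 50% versus 20%, the 95% half-width is 1.96 × √(0.5 × 0.5/21 + 0.2 × 0.8/9) = 0.338, about 34 percentage points. If 0 of 9 monitored patients respond, the exact 95% interval for the background rate still runs to 34%. At 1 of 9 it is 0.3% to 48%.

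**4. Can the two criteria disagree?** Take 10 of 21 treated, which passes the Simon bound of 8, and 1 of 9 monitored. There are 11 responders among 30, so the one-sided Fisher p is

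[C(19,9) + 11 × C(19,8)] / C(30,9) = (92,378 + 831,402) / 14,307,150 = 0.065.

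Adding the equally or less likely tables in the other tail (0.035) gives two-sided p = 0.10. The comparison fails on either footing.

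**5. Does the 90% hold for the Simon rule as the article runs it?** At a true rate of 50%:
- P(≤ 2 of 12) = 0.019
- P(3–5 of 12) = 0.368
- P(≥ 6 of 12) = 0.613
- Positive at ≥ 8 of 21 after ≥ 6 of 12: 0.608
- Positive at ≥ 8 of 21 after 3–5 of 12, if the trial continued to 21: 0.293

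The sum 0.608 + 0.293 = 0.901 recovers the stated power. The 0.293 is available only if a result of 3–5 of 12 goes on to 21 patients, whereas the article pauses there and re-estimates.

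**The case against.** The strongest reply is that this is an open-label, one-armed phase IIa trial with a mainly descriptive analysis. The 90% is tied explicitly to Simon's design, the stage 1 decisions use treated counts alone, and further detail is left to the statistical analysis plan. Much of this stands, and it rules out several stronger readings.

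- A reader might infer that the comparison simply has 29% power. The article does not support that. Its 20% is a no-merit threshold for treated patients, not an expected rate in monitored ones, and it names no Fisher test. The figure is the 20% row of a range from 29% to 81% two-sided.
- A reader might infer that the article claims 90% power for the comparison. It does not. It claims no power for it, which is the gap.
- A reader might cite 8 of 21 against 0 of 9 as proof of conflict. Two-sided p is 0.067, but one-sided p is 0.035, and Simon's rule is one-sided. On that footing the criteria agree, which is why 10 of 21 against 1 of 9 is the example used here.
- A reader might treat the comparison as within-patient. The nine probably overlap the 21, but at most 9 of the 21 can be paired. The overlap also makes the independent-groups power figures approximate.

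The descriptive label and the deferral to the analysis plan do not remove the point. The comparison is part of the primary endpoint's definition, and the mismatch lies between statements that are both in this article.

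**Conclusion.** The point holds. The primary endpoint and its analysis are a comparison with nine monitored patients, while alpha 0.05 and 90% power belong to a one-sample rule that the analysis section does not mention. The mismatch itself needs no assumption.

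Its size does rest on assumptions: 50% treated response, independent groups and a Fisher test at 5%. On those, power is 29% to 81% two-sided and 30% to 91% one-sided as the background rate falls from 20% to 0%. The comparison is weak over most of that range, and only the one-sided test at a background rate of zero reaches 90%. Since the background rate is unknown, no single power figure can be attached to the plan.

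The 90% is also conditional for the Simon rule itself, because it needs every stage 1 result of 3 or more of 12 to continue to 21.

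**What to change.** 1. Name one primary criterion: the one-sample Simon rule, null response rate at most 20%, activity declared at 8 or more of 21.
2. State that alpha 0.05 and 90% power apply to that test only, and only if every stage 1 result of 3 or more of 12 continues to 21 patients. Reconcile this with the pause and re-estimation at 3–5 of 12 in Sample Size calculation.
3. Present the comparison with the nine monitored patients as supportive estimation: a difference with its 95% confidence interval, no power claim, and a method that accounts for patients who are in both groups.
4. Reword Trial endpoints and Primary and secondary analysis to match.

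The cost is wording in the protocol and analysis plan, with no extra patients. The downside is that the control comparison loses primary status and its low precision is stated openly. The change should be made before stage 1 outcomes are seen.

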### Data Handling and management

Participant data will be pseudo-anonymised and will be stored on a password protected computer at each NHS recruiting site. The main dataset is the Elsevier Macro 4 EDC system dataset hosted by the King’s College Clinical Trial Unit. Baseline and follow up data will be collected onto source data worksheets, which will form part of the NHS medical notes. Clinical and research data will be transcribed from the medical notes and source data worksheets to the study eCRF system.

Data relating to the exploratory mechanistic endpoints will be treated differently. A copy of the raw unmanipulated data, labelled with data, PIN and type of analysis will be stored securely as soon as possible after obtained. Descriptive analyses will be prepared from cleaned data by the trial statisticians. Outlying data will be compared to raw data files for validation.

All trial data will be stored in line with the Medicines for Human Use (Clinical Trials) Amended Regulations 2006 and the UK General Data Protection Regulation (UK-GDPR) and UK Data Protection Act 2018 and archived in line with the Medicines for Human Use (Clinical Trials) Amended Regulations 2006 as defined in the Clinical Trials Office Archiving SOP.

### Data monitoring

Risk-based monitoring of this study to ensure compliance with Good Clinical Practice and scientific integrity will be managed by KHP CTO (King’s Health Partners Clinical Trials Office). A Data monitoring Committee including independant related members has been designated to oversee the monitoring of the study. A Trial Steering committee has been designated to provide overall supervision for the GAMECHANgER-1 trial on behalf of the Trial Sponsor and the Trial Funder and to ensure that the trial is conducted according to the guidelines for Good Clinical Practice (GCP), Research Governance Framework for Health and Social Care and all relevant regulations and local policies.

### Dissemination

Results from this study will be published in international peer-reviewed journal with high impact. They will be presented in national, international conferences and using social media. Recruiting sites will be informed of the results and will be asked to disseminate the findings to participants. Patient groups will be informed of the results for dissemination among their members.

## Discussion

The current dogma is that memory immune alloresponses cannot be modulated or suppressed by regulatory T cell [22, 23]. Data from our group [10–12] and others [9] have demonstrated that regulatory T cells could be able to modulate response to HLA in pre-sensitised individuals with CAMR, and that more importantly they are able to fine-tune the phenotype of B cells, allowing them to switch from APC to B cells with regulatory impact. Some recent breakthroughs, including Imlifidase [20] and FcRn antagonists [4], could change the outcomes of antibody incompatible transplantation in the future by targeting humoral responses, however there is no efficient therapy targeting memory immune alloresponses in these patients.

Infusion of polyclonally expanded Tregs has been demonstrated to be safe [8–11], however the ultimate aim in these initial studies was to induce tolerance. Our hypothesis is based on the idea that Treg infusions could modulate memory immune alloresponses. We propose to infuse GMP-grade in vitro expanded polyclonal Tregs into appropriate sensitised patients on the transplant waiting list. Appropriate in this context means those identified in an initial observational phase (Part 1) to have CD4^+^ T cell IFNγ or IL-17A FluoroSpot responses to a defined HLA without evidence of regulation by endogenous Tregs. The HLA antigens used will be those to which the recipient has Ab; to be clinically relevant, we will focus on Ab that could be delisted or be the focus of desensitisation. We anticipate that the Tregs will induce a reduction in the measurable response to the specific anti-HLA B cell-dependent T cell responses, which we will measure using purified HLA antigens in CD4^+^ T cell FluoroSpot assays.

Assuming we demonstrate that our strategy suppresses responses in significant proportions of patients, an important question is how long does the effect last? This will be evaluated using data from immune monitoring post-Treg infusion. We will use this information to model, with NHSBT, the impact of the new allocation scheme on numbers of highly sensitised patients, in conjunction with early data on their observed post-transplant outcomes. In addition, with the advent of novel therapies like Imlifidase [20] and FcRn antagonists [4], we will model the impact of delisting or desensitising significant numbers of new patients, to inform on the feasibility of performing a larger trial, with clinically relevant endpoints in these patients.

Our ultimate goal is to develop non-toxic immunotherapies capable of controlling cell-mediated B and T cell responses in these ‘highly sensitised’ patients to promote better graft and patient outcomes and ultimately better access to transplantation in this group. This trial will deliver the insights necessary to assess whether further clinical investigation / application of our solution is feasible.

### Trial status

This manuscript is based on protocol version2, 6/12/21. At the time of submission, the trial has recruited 31 patients to Part 1, after recruitment started in April 2022.

## Data Availability

Not applicable.

## Abbreviations

ATIMP: Advanced Therapy IMP
Ab: Antibodies
CRF: Calculated Reaction Frequency
CAMR: Chronic antibody mediated rejection
ESRF: End stage renal failure
FcR: FcReceptors
GMP: Good Manufacturing Practice
HS: Highly sensitised
HCV: Hepatitis C Virus
HBV: Hepatitis B Virus
HIV: Human Immunodeficiency virus
HLA: Human leukocyte antigens
KHP CTO: King’s Health Partners Clinical Trials Office
IFNγ: IFNgamma
IMPs: Investigational medicinal products
NHSBT: National Health Service Blood and Transplant
NIHR: National Institute for Health Research
PBMC: Peripheral blood mononuclear cells
Tregs: Regulatory T cells
Shla: Soluble HLA
UKTR: UK Transplant Registry
